We will use quantitative methods to evaluate the effectiveness of TG-DSD for viral suppression and prevention-effective adherence and to assess stigma and GAHT use as potential mediators. As noted earlier, our first hypothesis is that rates of viral suppression are more likely to increase among transgender people on ART at TG-DSD sites than among transgender people on ART at SSD sites over the 12-month study period.

The primary outcome measure is the proportion of transgender people on ART with viral suppression (HIV RNA <50 copies/mL). Descriptive analyses will summarize HIV viral suppression comparing participants at TG-DSD versus SSD sites as well as by gender identity at baseline and 12 months. Percent distributions will be computed for categorical variables and means, ranges, SDs, medians, and IQRs will be presented for continuous variables stratified by attendance at TG-DSD versus SSD sites. The primary estimate for this aim is the absolute difference in the change in proportion of virally suppressed during the study period between participants at TG-DSD sites and those at SSD sites. A difference-in-difference (D-i-D) analysis will be conducted to account for anticipated differences between groups at baseline (TG-DSD vs SSD). In addition, we will compare differences at 12 months considering baseline values to enhance the robustness of the estimators of the differences in the 2 groups.

A mixed-effects binomial model will be fit, where the binary viral load suppression status of each client is regressed on fixed effects for time (baseline vs 12 months), TG-DSD versus SSD site, the time by site model interaction, and client-level covariates (age and gender identity). In addition, random intercepts for each of the sites will be included in the model to account for within-site correlation. The D-i-D estimator is the estimated regression coefficient for the time by service delivery model interaction term. All models will account for clustering and be adjusted for relevant confounders in baseline covariates.

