The second hypothesis is that rates of prevention-effective adherence are more likely to increase among transgender people who are HIV negative at TG-DSD sites than among those at SSD sites, over the 12-month study period. We will follow the same steps outlined above for the primary hypothesis. However, we define the outcome measure (prevention-effective adherence) as the proportion of (1) participants on PrEP with TFV levels >700 fmol/punch and (2) participants who are not on PrEP who report no condomless intercourse during the prior 30 days. The estimate will be the absolute difference in the change in the proportion who achieve prevention-effective adherence during the study period comparing those at TG-DSD versus SSD sites. In addition, we will estimate the difference between TG-DSD and SSD sites at 12 months, considering baseline values.

Clients who receive SSD services on enrollment may switch to TG-DSD over time, thereby reducing the sample size of the SSD arm and creating a threat to internal validity. To identify and account for switches over time, we will update information about where the participant is receiving care at every study visit. Participants who transfer from an SSD site to a TG-DSD site will be censored after the date of their last visit for the primary analysis. It would be inappropriate and unethical to require participants to continue receiving care at a specific site, therefore we will use careful tracking to inform an exploratory dose-response analysis that considers the amount of time a participant received care at the TG-DSD sites. The amount of time receiving care at the TG-DSD site will be the independent variable, with the change in outcome from baseline to 12 months as the dependent variable.

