### Statistical Power

Power analyses and sample size calculations were based on the primary outcome of viral suppression (aim 2). No viral load data are available for transgender people in South Africa disaggregated from other key populations. The only South African data that includes transgender women and uses the current nationally recommended threshold for viral suppression includes cisgender men who have sex with men. Nonetheless, the study found a viral suppression rate of 47% [101]. One study of transgender people receiving TG-DSD in South Africa found that those on GAHT were 3 times more likely to be virally suppressed compared to transgender people who are not on GAHT [49]. This suggests an effect size of at least 20%. We consider an effect size as low as 15% to be clinically significant.

On the basis of the aforementioned data and clinical experience, we anticipate that current viral suppression rates will be approximately 65% at baseline, rising to 85% at 12 months among TG-DSD participants, and approximately 61% at baseline, rising to 66% at 12 months among SSD participants. This 20% difference from baseline to 12 months for TG-DSD participants and 5% difference from baseline to 12 months for SSD participants represents a difference in the absolute change in viral suppression rates of 15%. Using *r*=1, α=.05, power of 1− β=.80, and p_1_=viral suppression in the SSD and p_2_=viral suppression in the TG-DSD group and difference of p_2_ – p_1_=.15, the minimum sample per group will be 172 for both TG-DSD and SSD, for a total minimum sample size of 344. Adjusting for loss to follow-up of approximately 12%, a sample of ≥200 in each group, for a total of ≥400 transgender people on ART, provides adequate statistical power for planned analyses.

Loss to follow-up is a challenge for any longitudinal study. We will make every effort to minimize loss to follow-up by collecting multiple forms of contact, reaching out monthly to update contacts, collecting data in the field as well as the study site, and providing remuneration for study participation. We are enrolling a larger sample size than required by the power calculations to allow for potential loss to follow-up without loss of statistical power.

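### The primary estimate is defined as an absolute difference in change in proportions, but the estimator named for it is the raw interaction coefficient of a binomial mixed model with no stated link, which equals that difference only under an identity link

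*Protocol article*

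**What the plan says.** All of this stands in the protocol article under Data Analysis for Aim 2, apart from the planning rates.

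- **Target, hypothesis 1:** "The primary estimate for this aim is the absolute difference in the change in proportion of virally suppressed during the study period", comparing TG-DSD with SSD participants.
- **Model:** "A mixed-effects binomial model will be fit, where the binary viral load suppression status of each client is regressed on fixed effects", namely those of time, service model, their interaction, age and gender identity. In addition, "random intercepts for each of the sites will be included in the model".
- **Estimator:** "The D-i-D estimator is the estimated regression coefficient for the time by service delivery model interaction term".
- **Hypothesis 2:** "We will follow the same steps outlined above for the primary hypothesis", and again an absolute target: "The estimate will be the absolute difference in the change in the proportion who achieve prevention-effective adherence during the study period".
- **Planning rates (Statistical Power):** viral suppression is put at "approximately 65% at baseline, rising to 85% at 12 months among TG-DSD participants". The corresponding SSD figures are 61% and 66%. The section summarises these as a 15-point difference in absolute change.

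The article names no link function and no linear probability model. It describes no step from the coefficient back to probabilities.

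**The concern.** An interaction coefficient is a difference-in-difference on the scale of the model's link. It is a difference in percentage points only if the link is the identity. The usual link for a binomial mixed model is the logit. With that link the named estimator is a log ratio of odds ratios, and because of the random intercepts it is conditional on site. An analyst who followed the estimator sentence with a logit model would report, as the primary estimate, a quantity other than the one defined shortly before it. That number and its confidence interval could not be read against the 15-point planning difference. Hypothesis 2 inherits the same conflict.

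**Working it through.** **Inputs.** From Statistical Power: TG-DSD 0.65 to 0.85, SSD 0.61 to 0.66, minimum 172 per group. From Overall Approach to Data Analysis: two-sided α = 0.05. The link is not stated, so three links are compared.

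**1. The plan's own figure.** (0.85 − 0.65) − (0.66 − 0.61) = 0.20 − 0.05 = 0.15. This reproduces the 15 points.

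**2. The interaction coefficient at the same rates.** With link g, it is [g(0.85) − g(0.65)] − [g(0.66) − g(0.61)].

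| Link | Calculation | Coefficient | Meaning |
|---|---|---|---|
| Identity | 0.20 − 0.05 | 0.150 | absolute D-i-D, the stated target |
| Logit | (1.735 − 0.619) − (0.663 − 0.447) | 0.900 | log of 3.05 / 1.24, a ratio of odds ratios of 2.46 |
| Log | ln(0.85/0.65) − ln(0.66/0.61) | 0.189 | ratio of risk ratios of 1.21 |

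Only the identity link returns the target.

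**3. No fixed conversion exists.** Hold the logit coefficient at 0.900 and vary the baselines. Only the first row is the plan's; the others are assumed.

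| TG-DSD baseline | SSD | Implied TG-DSD at 12 months | Absolute D-i-D |
|---|---|---|---|
| 65% | 61% to 66% | 85.0% | 0.150 |
| 50% | 47% to 52% | 75.0% | 0.200 |
| 80% | 75% to 80% | 92.9% | 0.079 |
| 90% | 85% to 90% | 97.2% | 0.022 |

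**4. Conditioning on site.** The protocol gives no between-site SD. For assumed SDs of 0.3, 0.5 and 1.0 on the logit scale, the site-conditional coefficient that matches the planned marginal rates is 0.913, 0.937 and 1.042, against 0.900 with no site variation.

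**5. Do the two scales test the same null?** Take equal 5-point rises, so that the absolute D-i-D is zero, and compute the logit interaction. For illustration, use 172 per group, treat baseline and 12-month observations as independent and ignore clustering. The standard error is then √Σ[1/(172·p·(1 − p))] over the four cells.

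- Planned baselines: 65% to 70% against 61% to 66%. Coefficient 0.012, ratio 1.012, SE 0.322, z = 0.04. A nominal 5% test rejects 5.0% of the time.
- Off-plan TG-DSD baseline of 80%: 80% to 85% against 61% to 66%. Ratio 1.14.
- Off-plan TG-DSD baseline of 85%: 85% to 90% against 61% to 66%. Coefficient 0.247, ratio 1.28, SE 0.401, z = 0.62. Rejection 9.4%.

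In the other direction, a zero logit interaction with SSD 61% to 66% implies an absolute D-i-D of −0.003 when TG-DSD starts at 65%, and −0.018 when it starts at 80%.

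**The case against.** The strongest reply is that the contradiction depends on a link the article never names. Nothing under Data Analysis for Aim 2 says logit, logistic or odds ratio. Read with an identity link, the target and estimator sentences agree. A condensed article may properly leave the link and post-estimation steps to an analysis plan that is not shown here.

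This stands in part. Silence about the link is not the finding. But the article does more than stay silent: it fixes both the target and a rule for reading it off the model, and the two fit only under a link that is not the usual one. An analysis plan that used a logit link would have to contradict one of the two sentences.

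Three stronger readings are tempting and are not supported:

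- **That the test could be significant with no absolute effect, or that the signs could disagree.** Both are possible in principle. At the planned 65% and 61%, however, the signs can differ only within about 0.3 points of zero, and rejection under a zero absolute D-i-D stays at 5.0%. The 1.28 example needs a TG-DSD baseline of 85%, which in the protocol is the anticipated 12-month rate. That is a 24-point baseline gap against a planned 4.
- **That the scale costs power.** With 172 per group and independent observations, the planning rates give z = 0.900/0.349 = 2.58 (power about 73%) on the logit scale and 0.15/0.0689 = 2.18 (about 59%) on the absolute scale. The logit test is therefore not the weaker one. Both figures ignore within-person correlation and site clustering, so they show no harm.
- **That the cost per additional success could not be computed.** Data Analysis for Aim 3 draws on the data collected for Aim 2 and does not say that the regression coefficient is an input. The planned descriptive summaries by site type at baseline and 12 months also give the crude absolute D-i-D. What would be lacking is the adjusted estimate and its interval on that scale.

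**Conclusion.** The point holds as a mismatch between a stated estimand and a stated estimator, for hypotheses 1 and 2. Under the standard logit link, the rule as written returns about 0.90 (ratio of odds ratios 2.46) at the planning rates, where the defined primary estimate is 0.15. Site variation moves the coefficient further from its marginal value.

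The main damage is to the reported adjusted effect and its confidence interval. The null hypothesis tested is almost the same at the planned baselines. It diverges appreciably only if the groups start much further apart than 65% and 61%. That cannot be excluded: the protocol anticipates baseline differences, says that disaggregated viral load data are not available for this population in South Africa, and gives no planning baseline for hypothesis 2.

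The conclusion assumes a non-identity link. An explicit identity link would remove the conflict.

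**What to change.** For hypotheses 1 and 2, replace the sentence naming the coefficient as the D-i-D estimator by one of these:

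1. The estimator is the D-i-D of model-standardised marginal probabilities at the four time-by-service-model cells. Its 95% CI and p value are computed on that scale, by the delta method or a bootstrap, in a way that respects site clustering.
2. The model uses an identity link, stated explicitly, so that the interaction coefficient is itself the absolute D-i-D.

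The odds-ratio interaction may be reported as well, labelled as such.

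The cost is a change of wording and, for the first option, one post-estimation step. No data collection or sample size changes.

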## Methods

### Overall Study Design

Jabula Uzibone is an observational, multisite, mixed methods, and prospective implementation study. To meet the first aim, we will assess the implementation of TG-DSD models and SSD models at the facility level using standardized observation checklists at 8 facilities (1 DSD site and 1 SSD site per area in all 4 areas). We will examine implementation, acceptability, feasibility, and barriers to and facilitators of TG-DSD via key informant interviews (KIIs; n=6 per site) with health facility staff. At the client level, we will conduct in-depth interviews (IDIs) with 30 transgender people (15, 50% from DSD sites and 15, 50% from SSD sites) drawn from the longitudinal cohort enrolled for aim 2 described in the next paragraph.

To meet the second aim, we will enroll a cohort of ≥600 transgender people and follow them for 12 months. Of the transgender people enrolled, ≥400 (66.7%) will be transgender people living with HIV. This will include ≥200 (50%) who receive ART at TG-DSD sites and ≥200 (50%) who receive ART at SSD sites in the same area as the TG-DSD sites. We will also enroll ≥200 transgender people without HIV. This will include ≥100 (50%) participants without HIV at TG-DSD sites and ≥100 (50%) without HIV at SSD sites in the same area as the TG-DSD sites. Each participant will complete a quarterly survey to assess engagement in HIV prevention and care, changes over time in experiences of gender affirmation, and experiences of stigma.

For participants on ART, we will measure HIV RNA levels (ie, viral load) at baseline and 12 months. For participants on PrEP, we will measure tenofovir levels at baseline and 12 months. For participants who are HIV negative and not on PrEP, we will assess self-reported condomless sex. Prevention-effective adherence is defined as being HIV negative and meeting one of the following criteria: (1) adherent to PrEP based on tenofovir levels, (2) self-report of consistent condom use in the prior 30 days, or (3) self-report of no anal or vaginal sex in the prior 30 days. Table 1 presents a list of data collection activities organized by level of analysis, participant type, and month of enrollment.

**Table 1 table1:** Data collection activities by level of analysis, participant type, and month of enrollment.

Level			Participant, n (%)		Baseline		Months 3, 6, and 9		Month 12

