	**Client**			
		IDIs with transgender participants	Tell me about your experience receiving care at the site.	
		Survey with transgender participants	Intersectional stigma scale by Scheim and Bauer [77], Psychological Gender Affirmation scale by Sevelius et al [78], and GAHT use by self-report.	
		Laboratory test with transgender participants	HIV RNA level by serum analysis (for transgender participants on ART) and tenofovir level by DBS^i^ (for transgender participants on PrEP)	

^a^GAHT: gender-affirming hormone therapy.

^b^ART: antiretroviral therapy.

^c^PrEP: pre-exposure prophylaxis.

^d^KII: key informant interview.

^e^AIM: Acceptability of Intervention Measure.

^f^IAM: Intervention Appropriateness Measure.

^g^FIM: feasibility of intervention measure.

^h^IDI: in-depth interview.

^i^DBS: dried blood spot.

Qualitative interview (KII and IDI) recordings will be transcribed and translated into English. The transcripts, field notes, and narrative summaries will be uploaded into qualitative data management software, Atlas.ti (ATLAS.ti Scientific Software Development GmbH), to facilitate analyses. During regularly scheduled meetings, the study team will review field notes, transcripts, and summaries; discuss emerging themes; and revise interviewing and coding strategies, as needed.

Statistical analysis of quantitative data will be performed using Stata (StataCorp) and MPlus (Muthén & Muthén). Data exploration of key variables will be conducted to assess for implausible values and determine whether statistical assumptions (eg, normal distributions of data) for planned statistical analyses are satisfied. Categorical variables will be reported as frequencies and percentages, with means and SDs or medians and IQRs reported for continuous variables. Patterns of missing data will be examined, including testing for differences between participants with and without missing data. A series of sensitivity analyses will be conducted to evaluate the robustness of conclusions drawn from the primary models to departures from the missing at random assumption by comparing the magnitude of the primary effect. In the rare situation that >10% missing data is observed, we will use multiple imputation, as appropriate. We will specify 2-sided tests, .05 significance level (α=.05), and compute 95% CIs throughout.

### Qualitative Data Analysis for Aim 1

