**Figure 1 figure1:**
[figure not shown]
Structural equation model to test stigma and gender affirmation as mediators of relationships between service delivery type and HIV outcomes.

### Exploratory Analyses for Aims 1 and 2

We will conduct 3 exploratory analyses. First, using longitudinal data from baseline, 3, 6, 9 and 12 months, we will perform mixed-effects regression modeling to analyze changes in stigma scores, psychological gender affirmation scores, and GAHT use over time by service delivery model. Mixed-effects regression is most appropriate for clustered longitudinal data as it captures correlations of repeated measures using random effects that describe cluster-specific trends over time [100]. Second, as sample size allows, we will assess HIV outcomes by subgroups. The D-i-D model, used to test hypothesis 1 and hypothesis 2, will be fit separately for subgroups defined by (a) gender identity, (b) sex assigned at birth, (c) individual care facility, and (d) colocated versus stand-alone TG-DSD sites. Third, the association between 12-month HIV outcomes (viral suppression rates and prevention-effective adherence rates) and implementation metrics from aim 1 will be examined graphically for the 4 TG-DSD sites by plotting the HIV outcomes at each site versus mean scores on the AIM, IAM, and FIM, respectively.

The use of D-i-D analyses implicitly assumes that TG-DSD sites are either comparable with SSD sites (other than the DSD approach) or that we can readily adjust for any differences. However, if we find that groups differ on important characteristics, we will use inverse probability of treatment weighting to adjust for the covariates in the effect estimation to mitigate potential bias.

### Data Analysis for Aim 3

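### The site random intercept all but drops out of the primary D-i-D, so the stated model accounts neither for differing site trends nor for repeated measurement, and its standard error is wrong in a direction the protocol's figures do not settle

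*Protocol article*

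**What the plan says.** **Design.** The cohort comes from 8 facilities, "1 DSD site and 1 SSD site per area in all 4 areas" (Overall Study Design). Service model is therefore an attribute of the site.

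**Primary model.** Data Analysis for Aim 2 lists fixed effects for time, service model, their interaction, age and gender identity. It adds a random intercept per site as the device for within-site correlation and reads the D-i-D off the interaction coefficient. It then states "All models will account for clustering and be adjusted for relevant confounders in baseline covariates". For this model it names no participant effect, site-by-time effect, robust variance or small-cluster correction. Hypothesis 2 follows the same steps.

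**Error rate.** "We will specify 2-sided tests, .05 significance level (α=.05), and compute 95% CIs throughout" (Overall Approach to Data Analysis).

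**Planning rates.** Suppression in the TG-DSD arm is taken as "approximately 65% at baseline, rising to 85% at 12 months among TG-DSD participants". The SSD arm is assumed to move from 61% to 66%. The planned contrast "represents a difference in the absolute change in viral suppression rates of 15" percentage points (Statistical Power).

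**Subgroups.** Exploratory Analyses for Aims 1 and 2 would refit the same D-i-D model within subgroups, including "c) individual care facility, and (d) colocated versus stand-alone TG-DSD sites".

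**The concern.** The D-i-D compares how much 4 TG-DSD sites changed with how much 4 SSD sites changed. The clustering that matters is variation between sites in their change. A site intercept describes variation in level, which subtracts out. The article recognises cluster-specific trends, but only for its exploratory models of stigma, gender affirmation and GAHT use.

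The model also treats a participant's baseline and month-12 results as independent within site. Omitting site trends makes the standard error too small; omitting the pairing makes it too large. The confidence interval for the primary outcome could then be too wide or too narrow, and the protocol gives neither quantity needed to tell which.

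Separately, one facility delivers one service model, so a time-by-model interaction does not exist inside it.

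**Working it through.** **1. The plan's own sample size.** The minimum of 172 per group reproduces from 47% (the reference rate cited in Statistical Power) against 62%, by the pooled two-proportion formula n = [1.960·√(2p̄q̄) + 0.842·√(p₁q₁+p₂q₂)]² / d²:

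- p̄ = 0.545, so 2p̄q̄ = 0.4960; p₁q₁+p₂q₂ = 0.2491+0.2356 = 0.4847; d = 0.15.
- n = (1.380+0.586)²/0.0225 = 171.8, i.e. 172. Then 172/0.88 = 195.5, i.e. 196, rounded up to 200.

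A few other base rates also give 172, but the planning rates beside it do not (66% v 85% gives 80; 61% v 76% gives 150). A formula of this kind compares independent persons at one time point, so the sample size contains no allowance for sites.

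**2. Cancellation.** For a linear model with the same people at both times, (site effect + month 12) − (site effect + baseline) removes the site effect exactly. For the stated logistic model it was checked by simulation (600 null datasets per setting, 4 sites per arm, 44 completers per site). Raising the site-intercept SD from 0 to 0.5 logits left the empirical SD of the D-i-D at 0.323; the model SE was 0.321 and 0.329.

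**3. The two omissions in the fitted logistic model.** Site-intercept SD 0.5; site-by-time SD 0, 0.25, 0.5 logits:

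| | Type I error of stated model |
|---|---|
| No within-person correlation | 3.8%, 7.3%, 19.0% |
| Strong within-person correlation (participant SD 2 logits) | 2.0%, 2.5%, 7.2% |

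A t test on site-level changes stayed between 4.7% and 6.2% throughout.

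**4. The same on the percentage-point scale (linear approximation).** Assumed: 43 completers per site (172 per arm), within-person correlation φ = 0.47, between-site SD of change τ. Null: 61% to 66% in both arms.

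- Unpaired variance: 2·(0.2379+0.2244) = 0.9246; SE = √(0.9246/172) = 0.0733.
- Paired variance: 0.9246 − 2·(2·0.47·√(0.2379·0.2244)) = 0.4902; SE = √(0.4902/172) = 0.0534.
- True SE = √(0.4902/172 + 2τ²/4) = 0.0534, 0.0574, 0.0640, 0.0778 for τ = 0, 3, 5, 8 points.
- Type I error = 2[1 − Φ(1.96·SE used / true SE)].

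| τ (points) | As written (unpaired) | Paired, no site-by-time term | t on 8 site changes, 6 df (simulated) |
|---|---|---|---|
| 0 | 0.7% | 5% | about 5% |
| 3 | 1.2% | 7% | about 5% |
| 5 | 2.5% | 10% | about 5% |
| 8 | 6.5% | 18% | about 5% |

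Simulation of the same setting agrees: about 1%, 1%, 2%, 6 to 7% as written; about 5%, 7 to 8%, 10%, 17 to 19% with pairing.

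**5. Power at the 15-point effect (planning rates).** Unpaired variance 0.2275+0.1275+0.2379+0.2244 = 0.8173, SE 0.0689; paired variance 0.4400, SE 0.0506. At τ = 0:

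- As written: Φ((0.15 − 1.96·0.0689)/0.0506) = Φ(0.30), about 60%.
- Paired z test: Φ(0.15/0.0506 − 1.96) = Φ(1.00), about 84%.
- t on 6 df: 67 to 70%, falling to about 63% at τ = 3 and 52 to 53% at τ = 5 (simulated and noncentral t).

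**6. One facility.** The columns for intercept, time, model and time × model have rank 2 of 4, because model is constant. The interaction cannot be estimated. A one-area D-i-D (43 per arm) can be, with a 95% half-width of 1.96·√(0.4400/43) = 0.198, about 20 points from sampling error alone. With one site per model, site trend cannot be separated from service-model effect.

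**The case against.** **A reader might infer that the plan has an inflated type I error.** The documents do not support that. The 7%, 10% and 18% figures, and the 84% power, belong to a paired model the protocol does not state. At φ = 0.47 the stated model is conservative at SDs of 0 to 5 points and only slightly above 5% at 8. Inflation of the stated model over most of the range requires little within-person correlation. This objection stands and limits the claim to a wrong standard error of unsettled direction.

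**A reader might infer that clustering is ignored everywhere.** That is too broad. The same section also plans a month-12 comparison that takes baseline into account, where a site intercept does not cancel. The point is confined to the D-i-D, which is the primary estimate.

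**Details of random effects may sit in an analysis plan that is not shown.** That would excuse silence. Here the article names the random effect, its purpose and the estimator, and that combination does not do what is promised.

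**A reader might infer that both subgroup analyses return nothing.** This holds only for the single-facility analysis read literally. The area pairing makes it natural to include SSD partners in the colocated versus stand-alone comparison; the text simply does not say so. Both are exploratory and conditional on sample size.

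**Conclusion.** The concern holds in this form: the stated primary model does not account for clustering in the D-i-D, because its one random effect nearly cancels and it omits both site-by-time variation (4 sites per arm) and within-person correlation. Under φ = 0.47 and a site SD of change of 0 to 8 points, type I error runs from about 1% to 7% as written, with about 60% power at SD 0. Adding pairing alone would move it to about 5% to 19%, so a half-repair would be worse than none for error control.

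φ and the site SD are assumptions, and the percentage-point figures rest on a linear approximation to the logistic model. The cancellation and the rank deficiency within one facility do not depend on those values, although cancellation is exact only in the linear case. The point governs inference on the primary outcome and should be corrected before analysis.

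**What to change.** **Primary inference (either option):**

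- Compare the 8 site-level changes in proportion, TG-DSD against SSD, with a t test on 6 df. This handles both omissions and is on the absolute-difference scale of the stated estimand. Adjustment for age and gender identity would be made at participant level before forming the site changes.
- Or add both a participant random effect and a random site-by-time effect, with a small-cluster reference distribution. Satterthwaite or Kenward-Roger degrees of freedom apply only if a linear model on participant change is used.

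Apply the same choice to Hypothesis 2.

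**Subgroups (Exploratory Analyses for Aims 1 and 2):** replace individual care facility by area (the TG-DSD/SSD pair). State that the colocated versus stand-alone analysis includes the SSD sites of those areas. Report both as exploratory.

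**Cost:** wording and a model option, with no new data. Intervals will be wider than from a paired z test when site trends differ. Power for 15 points is about 67 to 70%, 63% and 52 to 53% at site SDs of 0, 3 and 5 points. That exceeds the stated model's roughly 60% at SD 0 and falls below it by SD 5.
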